### Association of Circadian Clocks and Alcoholism

In recent years evidence emerged that there is a bidirectional relationship between circadian rhythms and alcohol consumption (15). AUD patients often suffer from circadian misalignment, which, in turn, is known to increase the risk of developing AUD (15–17).

On the one hand, individuals with AUD almost always suffer from disorders of the circadian system, such as disturbed sleep times, impaired sleep quality, altered molecular rhythms, and altered daily rhythms of neuroendocrinological functions in different regions of the brain (18). Even acute alcohol drinking can cause spontaneous alterations in circadian rhythms (19), and circadian rhythms are also affected during alcohol withdrawal (20, 21). Importantly, alcohol-dependent patients have a higher risk of relapse during withdrawal if their internal clock is disturbed (18). On the other hand, disrupted circadian rhythms are considered a strong risk factor for the development of AUD, as disturbances of circadian sleep-wake cycles are frequently observed in subjects with a late chronotype and shift workers show an increased prevalence of harmful use of alcohol and AUD (19). Moreover, single nucleotide polymorphisms in the clock genes Clock, Per2, and Per3 genes have been associated with alcohol consumption behavior (22, 23).

Curiously, although AUD patients generally suffer disturbances of molecular and behavioral rhythms, their need for alcohol often follows circadian patterns with around 80% of alcohol addicts having their first drink at a specific hour with low variability (17, 24–27). Accordingly, in rodents, the regular administration of drugs can trigger anticipatory locomotor activity before the drug is actually provided, which suggests the existence of a drug-entrainable oscillator (24).

In summary, AUD patients have disturbed circadian rhythms in daily sleep and neuroendocrinological rhythms on the one hand, but on the other hand are strongly entrained by alcohol. Together, these data highly suggest an imbalance of *Zeitgeber* signals in AUD patients. While light, food, and physical activity are usually the strongest *Zeitgebers*, in AUD patients these may lose influence and be replaced by alcohol. Thus, a targeted amplification of the other *Zeitgebers* can possibly reduce the influence of the *Zeitgeber* alcohol and thereby reduce symptoms of AUD patients during withdrawal and help to reduce relapses.

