Furthermore, at this meeting the test persons are again made aware of the importance of very regular eating and sleeping times. If the test diary shows that the test person has lived rather irregularly, solutions are developed for maintaining more daily regularity. This session also serves as an opportunity to answer potential questions from the study participants and to remind them of the importance of adhering to the daily structure plan that has been drawn up. Participants receive new blank diaries which they are asked to fill in for the next 4 weeks. The times of the designed daily structure plan are handwritten in the empty diary pages as a visual support for precise adherence to the times.

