## Measured Outcomes

Our primary hypothesis is that a regular exposure to *Zeitgebers* stabilizes circadian behavioral rhythms and thereby reduces the risk of alcohol relapses in AUD patients. Therefore, the first primary outcomes of the study are the Routine Variability Score and drinking behavior of each individual test person. For generation of the Routine Variability Scores, first, day-to-day variability will be calculated from the following parameters: bedtime, wake-up time, sleep quality, time of getting-up in the morning, time to go to bed in the evening, lights-off time, breakfast time, lunch time and dinner time. The individual Routine Variability Score is comparable to the validated social rhythm metric scale (SRMS) (66) and will be calculated as follows (example for bedtime): For the period of 1 week, the average bedtime will be calculated. Then the deviation from this average bedtime is calculated in minutes for each day. These deviations are summed up and the mean value is calculated. This mean value will be coded according to the magnitude of time variability: 1: 0–15 min, 2: 16–30 min, 3: 31–45 min, 4: 46–60 min, 5: 61–75 min, 6: 76–90 min, 7: 91–105 min, 8: 106–120 min, 9: 2–3 h, 10: 3–4 h, 11: over 4 h (67). This way a separate score can be created for each parameter collected in the diary. These scores can be calculated on a weekly basis to examine whether relapses or deterioration in well-being are related to irregularities in the daily routine during that week, or over the duration of the entire survey phase to check how regularity over a longer period is related to drinking behavior and well-being. In addition, the scores for sleep and meals, for example, can be calculated individually to examine their influence on drinking behavior and well-being separately.

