Additionally, a questionnaire specially designed for this study with a total of 30 questions and a 4-step ordinal scale for the answers to assess the rating of the participants' subjective structuredness in their everyday life will be filled out. This questionnaire includes, for example, questions on the subjective assessment of whether activities such as eating, sleeping and sport are carried out regularly, whether relapses are associated with irregular daily routines, and whether the craving for alcohol usually occurs at the same time of day. To give the subjects of the control group no indication of the actual aim of the study, the questions that aim at the circadian daily structure are mixed with neutral questions.

Drinking behavior and daily craving will be assessed with questionnaires and the diary, respectively (Table 1). General drinking habits of the last few weeks are surveyed using the AUDIT questionnaire. In addition, the European Addiction Severity Index (EuropASI) is used, which covers not only alcohol and drug consumption but also physical, psychological, financial, and social problem areas of addicted patients. The number of alcoholic drinks and the number of alcohol-free days within the past 30 days is assessed by means of the Timeline Followback 30 (TLFB-30). The diary, which the subjects fill out to collect the Routine Variability Scores, additionally records the highest craving for alcohol on a scale of 0–10 of each day.

According to our secondary hypothesis that the stabilization of circadian rhythms contributes to the reduction of depressive symptoms and increased well-being, changes in the affective state, with a focus on depressive symptoms, are measured with the external assessment questionnaire Hamilton Depression Scale (HAMD) and with the self-reporting questionnaire Inventory of Depressive Symptomatology (IDS-SR). Sleep quantity and quality will be assessed by Pittsburgh Sleep Quality Index (PSQI). Furthermore, for measuring if the DAILY structure program will influence the feeling of self-efficacy, we will employ the Generalized Self-Efficacy Scale (GSES).

As exploratory outcomes, it will be documented how many subjects in the DAILY intervention group and the control groups discontinue the therapy. Furthermore, possible changes of the chronotypes in the course of the study will be defined by the Munich ChronoType Questionnaire (MCTQ).

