## Data Analysis

All statistical analyses will be performed using SPSS software version 25 (SPSS INC., Chicago, IL, USA). Sociodemographic data, chronotype, diary data and blood parameters will be reported in form of descriptive statistics. Continuous variables will be presented as mean ± *SD* and normality of continuous data will be measured by using the Kolmogorov-Smirnov-Test. Accordingly, we will use parametric and non-parametric analyses. For all calculations, the significance level will be determined at α < 0.05.

Data analysis will be performed according to intention-to-treat analysis (ITT) rules. In particular, this means that all subjects who completed the questionnaires of the first session and the 1st week of the diaries are included in the analysis, regardless of whether their subsequent data sets are complete or whether they have dropped out of the study. This is done by imputing missing data with the help of all available data that was assessed until then. Participants who withdraw their consent and were not assessed with baseline measurements will be treated as dropouts. All other subjects regardless from the study condition will be analyzed according to ITT.

The data will be evaluated in three different ways: First, outcomes of the endpoint of the study will be compared between the intervention and control groups using unpaired group analyses (e.g., Student's *t*-test, Mann-Whitney *U*-test, Kruskal-Wallis test, one-way ANOVA). Secondly, within-subject analyses of the intervention and control groups are performed, comparing the changes between the start and end of the study of the two groups (e.g., two-way ANOVA). Thirdly, the data are calculated independently of group membership in two-dimensional linear regression using the Routine Variability Scores as an independent variant.

Additionally, statistical differences in the frequency of dropouts between the two groups are calculated using chi-square tests and survival analyses. Multiple regression analyses will be applied to investigate the degree to which predictor variables (i.e., Routine Variability Scores, depression level, severity of alcohol consumption behavior, and self-efficacy score) contribute to outcomes of primary and secondary measures.

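### The pooled regression on same-period Routine Variability Scores cannot separate an effect of regularity on drinking from the effect of drinking on regularity that the protocol itself describes

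*Protocol article*

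**What the plan says.** The Data Analysis section lists three evaluations: a between-arm comparison at the endpoint, a comparison of change between start and end in the two arms, and a third in which "the data are calculated independently of group membership in two-dimensional linear regression using the Routine Variability Scores as an independent variant". Two-dimensional means one predictor and one outcome, so leaving arm out is a stated choice.

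Measured Outcomes gives the timing. Weekly scores serve "to examine whether relapses or deterioration in well-being are related to irregularities in the daily routine during that week". The alternative is a score taken "over the duration of the entire survey phase to check how regularity over a longer period is related to drinking behavior and well-being". The section then says that sleep and meal scores can be taken separately to study their influence on drinking.

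The drinking measure covers the same period. For the Timeline Followback, "The number of alcoholic drinks and the number of alcohol-free days within the past 30 days is assessed" at the last session. The diary that feeds the score runs through the four weeks before it: "Participants receive new blank diaries which they are asked to fill in for the next 4 weeks".

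Under Association of Circadian Clocks and Alcoholism, the protocol calls the relationship bidirectional and adds: "Even acute alcohol drinking can cause spontaneous alterations in circadian rhythms".

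The multiple regressions at the end of Data Analysis use the Routine Variability Score together with "depression level, severity of alcohol consumption behavior, and self-efficacy score) contribute to outcomes of primary and secondary measures".

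**The concern.** The primary hypothesis is causal: regular Zeitgebers stabilise rhythms and by that route reduce drinking and relapse. A regression with the score as predictor and drinking as outcome looks like a test of that link. But a drinking episode can also shift bedtimes and mealtimes in the same week. A positive same-period slope is then expected whether or not regularity protects against drinking.

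Leaving out arm adds a second route. The Discussion names psychological benefits, such as a feeling of stability and control, as a component of DAILY alongside circadian strengthening. If DAILY lowers both the score and drinking by different paths, the pooled slope absorbs this.

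The multiple regressions have a related problem. Their predictors are also primary or secondary outcomes, and the text does not say from which visit they come. As worded, a final-visit outcome could be regressed on a same-time version of itself.

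At stake is how the pilot is read. Its stated purpose is to find the best options for a main trial, and an artefact of reverse causation could be taken as support for the mechanism.

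**Working it through.** **No plan figure to reproduce.** The Design section states that every eligible patient within the year is included without a power calculation. Sample sizes and effect sizes below are assumptions. Alpha is 0.05 (Data Analysis), taken as two-sided.

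**Step 1: overlap of the windows.** The diary covers 4 × 7 = 28 days before the last session and the Timeline Followback covers 30. So 28/30 = 93% of the drinking window is also the score window.

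**Step 2: the slope when regularity has no effect.** Let drinking be D ~ N(0,1) and let the score respond only to drinking: V = b·D + √(1−b²)·e, with e ~ N(0,1). The slope of D on V is Cov(D,V)/Var(V) = b/(b² + 1 − b²) = b. It should be 0 if it measured the effect of regularity, and it does not shrink as N grows.

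**Step 3: how often p<0.05.** Simulation, 5,000 runs per cell, pooled simple regression of D on V:

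| Total N | b=0 | b=0.2 | b=0.3 | b=0.5 | Randomised arm comparison of D |
|---|---|---|---|---|---|
| 20 | 5.2% | 13.5% | 25.9% | 63.6% | 5.1% |
| 30 | 4.8% | 20.0% | 36.2% | 83.1% | 4.9% |
| 40 | 5.0% | 24.2% | 49.1% | 91.9% | 4.3% |
| 60 | 5.0% | 34.4% | 65.4% | 98.7% | 5.1% |
| 100 | 5.2% | 51.7% | 87.1% | 100% | 4.6% |

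Check by Fisher's z: power ≈ Φ(atanh(b)·√(N−3) − 1.96). For b=0.3 and N=40 this is Φ(0.3095 × 6.083 − 1.96) = Φ(−0.08) = 47%, against 49% simulated. Letting DAILY lower the score by 0.5 SD, with b=0.3, leaves the rates similar (24% at N=20 to 84% at N=100).

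**Step 4: the protocol's own 1–11 coding.** Assumptions: four weeks; 26 or 43 patients; 12% weekly relapse independent of the score; patient mean deviation lognormal with median 45 min and log-SD 0.35; weekly log-SD 0.25; a relapse adds a fixed number of minutes to that week's mean deviation. 1,500 trials per cell. Repeat runs differ by a few percentage points.

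| Minutes added by a relapse | Same week, stacked | One whole-phase score per person |
|---|---|---|
| 0 | 4–5% | – |
| 5 | 11–14% | – |
| 15 | 57–61% (N=26), 81% (N=43) | 10–14% |
| 30 | 98–100% | 25–38% |

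With 0 minutes the same-week rate is nominal, so the excess comes from the reverse path.

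**Step 5: does a lag help?** Regressing next week's relapse on this week's score gives 4–6% in that model. This holds because every patient was given the same relapse risk. If risk varies strongly between patients (beta-distributed, mean 12%, concentration 2), the unadjusted lag gives 15–19% at 15 min and 27–35% at 30 min. A lag therefore needs adjustment for the earlier week's outcome. That adjusted model was not simulated.

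**The case against.** The strongest reply is that this evaluation comes third of three, in a pilot, and is partly worded as a relation and not as an effect. The first two evaluations compare randomised arms, and both the score and drinking are outcomes there. That reply stands as far as it goes: the arm comparison of drinking held its nominal level in step 3. It does not rescue the regression, because the text also speaks of influence, the hypothesis is causal, and the limitations do not mention reverse causation.

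A second reply is that the size depends on invented inputs and that the whole-phase version is much milder. This also stands, and is why only ranges are given.

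Stronger readings that a reader might infer are not supported:

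- That the regression will be significant. Only the expected slope is shifted.
- That linear regression is applied to yes/no relapse, or that weeks from one patient are treated as independent. Data Analysis names no outcome for this regression and does not say that weeks are stacked. Measured Outcomes has quantitative measures (drinks, alcohol-free days, craving 0–10).
- That this is the only analysis of the mechanism. The multiple regressions bear on it too, and the arm comparison of the score tests its first link.
- That the Timeline Followback already gives drinking by date. The article reports 30-day counts, and the diary items listed include craving but not drinking.

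Predictor timing and clustering may be left to a fuller document. The one-predictor model without arm and the same-period pairing are written choices.

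**Conclusion.** The concern holds in a limited form. The regression as described cannot distinguish regularity reducing drinking from drinking disrupting regularity, and the protocol asserts that the second occurs. The bias is in the slope and does not diminish with sample size.

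With no effect of regularity, the chance of p<0.05 is roughly 10–40% for one whole-phase score per person (15–30 min added by a relapse) and about 11–100% for stacked same-week data (5–30 min added). Smaller disturbances bring both towards 5%. These figures rest on the assumed sample sizes, relapse rate and disturbance. The extra bias from omitting arm was not quantified.

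A reader might conclude that the trial's efficacy results are compromised. They are not: the randomised comparisons of score and drinking stand. What should change is the analysis and reading of the regressions.

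**What to change.** 1. Include arm in the same-period regression and report it as a descriptive association, without the language of influence.
2. For any directional statement, relate the score in one week to the outcome in the following week: drinking where it is dated, otherwise diary craving. Adjust for arm and for that outcome in the earlier week, with patient as cluster and few covariates. Even then, report an association, because the score is not randomised.
3. In the multiple regressions, use baseline depression, drinking severity and self-efficacy plus arm, so that no outcome is regressed on a same-time version of itself.

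A larger logistic model for lagged relapse would be too heavy. At the assumed 12%, three lagged weeks give 26 × 3 × 0.12 ≈ 9 to 43 × 3 × 0.12 ≈ 15 events. Four terms would then have about 2 to 4 events each.

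The cost is mainly wording. One week per patient is lost to the lag, and precision will be low in a pilot. Weekly drinking must be dated, which the weekly relapse analysis in Measured Outcomes already requires.

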## Study Hypotheses and Objectives

Our primary hypothesis is that a regular exposure to *Zeitgebers* stabilizes circadian behavioral rhythms and thereby reduces alcohol consumption and the risk of alcohol relapses in AUD patients. Accordingly, the primary objectives of the study are to determine whether the intervention program DAILY decreases day-to-day variations in behavior and reduces alcohol consumption and the relapse rate in AUD patients compared to those receiving control treatment. Furthermore, we hypothesize that the regular exposure to *Zeitgebers* contributes to the reduction of depressive symptoms and a subjective and physiological well-being in AUD patients, which in turn positively affects the primary objectives of the study. Accordingly, the secondary objective of the study is to ascertain whether the DAILY program supports the surrogate criterions of increased sleep quality, reduced depressive symptoms, increased self-efficacy expectations, and improved blood-values that are associated with harmful alcohol consumption. We also hypothesize, that additional psychoeducation about biological mechanisms in the development of AUD helps participants to complete their current therapy and maintain compliance. Therefore, as exploratory outcomes, we will investigate whether more participants of the intervention group accomplish the DAILY therapy than participants of the control group. Finally, we will assess whether the DAILY intervention has impact on the chronotype of the participants, although it is not a specific aim of our treatment to change it.

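### The additional multiple regression explains trial outcomes by other trial outcomes, with no time point and without treatment arm among the listed predictors, so its coefficients show association only and not contribution to outcome

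*Protocol article*

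**What the plan says.** The Data Analysis section of the protocol article first sets out three evaluations. The first is the between-arm test: "First, outcomes of the endpoint of the study will be compared between the intervention and control groups using unpaired group analyses". The second compares change over the study in the two groups. The third deliberately ignores arm: "Thirdly, the data are calculated independently of group membership in two-dimensional linear regression using the Routine Variability Scores as an independent variant".

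After a comparison of dropout, a further analysis is added: "Multiple regression analyses will be applied to investigate the degree to which predictor variables", with the predictors and dependent variables given as "i.e., Routine Variability Scores, depression level, severity of alcohol consumption behavior, and self-efficacy score) contribute to outcomes of primary and secondary measures". The same section applies one significance level throughout: "For all calculations, the significance level will be determined at α < 0.05".

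Measured Outcomes states that "the first primary outcomes of the study are the Routine Variability Score and drinking behavior of each individual test person". Study Hypotheses and Objectives lists the secondary criteria as "increased sleep quality, reduced depressive symptoms, increased self-efficacy expectations, and improved blood-values". Measured Outcomes names the self-efficacy scale as the instrument "for measuring if the DAILY structure program will influence the feeling of self-efficacy".

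**The concern.** The regression asks which factors contribute to outcome, yet each listed factor is something the trial treats as a result. Three difficulties follow.

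- **No time point.** The questionnaires are given at the first and last sessions, so a predictor could be a first-session value, a last-session value or a change. Only the first gives an ordinary prognostic model.
- **No arm in the list.** A predictor measured after treatment has begun can be moved by arm. If arm also moves the outcome, the two correlate even when neither influences the other.
- **Same construct on both sides.** Drinking is measured by AUDIT, EuropASI and TLFB, and depression by HAMD and IDS-SR. Explaining one instrument by another of the same construct measures their agreement.

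At stake is the trial's mechanistic idea that steadier routines lead to less drinking. A significant Routine Variability Score in this model is likely to be cited in its support, and the model as described cannot carry that weight.

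**Working it through.** **1. Predictors set beside outcomes**

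| Listed predictor | Role elsewhere in the article | When available (Table 1) |
|---|---|---|
| Routine Variability Score | Primary | Diary, between sessions only |
| Severity of alcohol consumption | Primary (drinking behavior) | First and last session |
| Depression level | Secondary | First and last session |
| Self-efficacy score | Secondary | First and last session |

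All four are outcomes. Sleep quality and blood values are outcomes that are not predictors.

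**2. The Routine Variability Score has no pre-treatment value.** Under Week 1 of the Intervention Group section, the diary is handed out at the end of the psychoeducation session, and participants are asked to look for their own patterns and follow them. Control participants get different session content. Even the first diary week is therefore open to the effect of arm.

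**3. How much arm alone can produce.** The article states no sample size. A rough bracket comes from Study Population (3 to 5 patients at once) and six weeks each over one year of recruitment: 3 × 52/6 = 26 and 5 × 52/6 = 43.3, taken as 44. Assume equal arms, an arm effect d1 (in SD) on regularity and d2 on drinking, and no link between the two within arms. Pooled over arms, the induced correlation is

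r = (d1·d2/4) / √[(1 + d1²/4)(1 + d2²/4)]

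- d1 = 0.8, d2 = 0.5: 0.10 / √(1.16 × 1.0625) = 0.09
- d1 = 1.2, d2 = 0.8: 0.24 / √(1.36 × 1.16) = 0.19

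Simulated least-squares fits, two-sided 0.05 (10,000 per setting), share with a significant regularity term:

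| N | d1, d2 | Without arm | With arm |
|---|---|---|---|
| 26 | 0.8, 0.5 | 7% | 5% |
| 26 | 1.2, 0.8 | 16% | 5% |
| 44 | 0.8, 0.5 | 9% | 5% |
| 44 | 1.2, 0.8 | 24% | 5% |

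With three further unrelated predictors in the model, the range without arm is 7 to 23%.

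**4. Different outcomes as same-time predictors.** Take four end-of-study outcomes with pairwise correlation c, each regressed on the other three without arm. With no DAILY effect, the chance of at least one significant predictor in one model is:

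| c | N = 26 | N = 44 |
|---|---|---|
| 0 | 0.13 | 0.14 (nominal 1 − 0.95³ = 0.143) |
| 0.1 | 0.17 | 0.23 |
| 0.3 | 0.39 | 0.56 |
| 0.5 | 0.56 | 0.81 |

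At c = 0.3, a DAILY effect of 0.5 SD on all four outcomes changes 0.39 and 0.56 only to 0.42 and 0.63. Significant predictors therefore say almost nothing about DAILY.

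**5. Same-construct pairs.** If two instruments correlate at an assumed 0.5 to 0.8, the same-construct term is significant in 0.57 to 0.99 of fits at N = 20 and in 0.91 to 1.00 at N = 40. This is power to detect an assumed true correlation, not a false-positive rate. It shows only that such a term will usually appear.

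**6. Adding arm alone is not enough.** With end-of-study predictors, N = 44, c = 0.3 and a 0.5 SD effect, the arm term is significant in 11% of fits, against 34 to 36% for a plain t-test, because the other outcomes absorb the effect. With baseline predictors plus arm (assumed baseline-to-end correlation 0.6), it is significant in 50%.

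**The case against.** The regression is an additional analysis and is not the test of DAILY. That job belongs to the endpoint and change comparisons between arms. A predictor analysis need not fall silent when treatment fails. The text nowhere says that last-session values will be used. With first-session questionnaire values this would be standard prognostic modelling, and an article may leave such detail to an analysis plan. The article also uses *i.e.* loosely elsewhere, so the list may not be closed and arm might still be added.

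Much of this stands, and it rules out several stronger readings that a reader might infer:

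- *The regression undermines the efficacy result.* It does not, because the between-arm comparisons do not depend on it.
- *The Routine Variability Score is regressed on itself.* The natural reading is that a variable leaves the predictor list when it is the outcome.
- *Predictors will be found almost regardless.* The frequency depends on N and on correlations the article does not give. At a correlation of 0.1 it is only 0.17 to 0.23 per model.
- *Baseline associations would be spurious.* They would be genuine prognostic associations.

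What the objection does not remove is the Routine Variability Score. It is named as a predictor and cannot be a first-session value, so the charitable baseline reading is not open for the one variable that carries the trial's hypothesis. Nor does the text stop one instrument from explaining another of the same construct.

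**Conclusion.** The point holds as a limit on interpretation. The regression draws its predictors from the trial's own outcomes, fixes no time point and does not list arm. Its coefficients cannot support a statement that these factors contribute to outcome. For regularity, arm alone can raise the false-positive rate from 5% to between 7 and 24%. That range rests on assumed arm effects of 0.8 to 1.2 SD on regularity and 0.5 to 0.8 SD on drinking, no link within arms, and 26 to 44 patients. With smaller arm effects the excess shrinks, and with none it disappears. Including arm restores about 5% in this setting. It does not settle direction: drinking may disturb routines as well as the reverse, and the Background itself describes a two-way relation. The correction is worth making, but it concerns a supplementary analysis and leaves the treatment comparison intact.

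**What to change.** Amend the multiple-regression sentence in Data Analysis as follows:

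1. Include randomised arm in every model.
2. Use first-session values for the questionnaire predictors (depression, alcohol severity, self-efficacy).
3. For each outcome, drop predictors of the same construct. The outcome's own first-session value may stay as a covariate but is not interpreted as a contributor.
4. Where the Routine Variability Score is used, whether for the first diary week or the whole phase, state that it is measured after randomisation, keep arm in the model, and report the result as exploratory and associational. Choosing the first week does not make it a baseline value.

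This keeps the aim in Measured Outcomes of relating regularity over a longer period to drinking, with a more modest claim. All the values are already collected, so the cost is wording, one degree of freedom per model for arm, and probably fewer significant predictors.
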